### Interventions

This research encompasses the evaluation of two investigation products that are supplied by KL-Kepong Oleomas Sdn Bhd. The first product, known as DavosLifeE3 Complete (50 mg), contains 50 mg of tocotrienols that are sourced from palm oil and meets the specifications outlined in the US Food and Drug Administration “generally recognized as safe” exemption claim 21 CFR 170.36 (c) [98]. The second product, Placebo Softgel, is a palm oil supplement that has the vitamin E compounds stripped off, serving as a vital control within the study. The blinding of the supplement is performed such that each group is labelled with their respective intervention product (IP) number without disclosing the content in the softgel. The softgels for both groups are odorless, of similar size and shape, and packaged in a fully opaque bottle. Contract research assistants generated the random allocation sequence, enroll participants, and assign participants to the interventions. Study participants, researchers, and data analysts will remain blinded throughout the clinical study to maintain blinding integrity throughout the 6-month intervention period.

### Outcomes

The study outcomes are divided into primary and secondary end points. The primary end points include vascular health (arterial stiffness), blood biochemistry (liver function, lipid profile, renal function, full blood count, and fasting glucose), oxidative stress (F2-IsoPs, MDA, AGEs, and PC), inflammation markers (TNF-α and IL-6), appetite regulation (ghrelin and leptin), and skin assessment (elasticity, hydration, transepidermal water loss, pigmentation, sebum secretion, wrinkles, and roughness). Meanwhile, cognitive function (Montreal Cognitive Assessment [MoCA], Rey Auditory Verbal Learning Test [RAVLT], and digit span test) and bone density fall under the secondary outcome measures.

The study encompasses a multifaceted array of assessments and procedures (Figure 1). For primary outcome measures, blood samples (15 mL) are collected as baseline samples for blood biochemistry analyses. Venous blood samples are drawn from the antecubital vein between 8 AM and 10 AM, following an 8- to 10-hour overnight fast. The standardized timing and fasting procedure are followed throughout all study visits (baseline, 3 months, and 6 months) to reduce biological variability caused by circadian rhythms and postprandial effects. After at least 5 minutes of rest to stabilize hemodynamic parameters before sampling, participants are seated, and blood is collected using sterile procedures.

**Figure 1 figure1:**
[figure not shown]
Overview of assessments and procedures for the 6-month clinical trial. DEXA: dual-energy X-ray absorptiometry; MoCA: Montreal Cognitive Assessment; RAVLT: Rey Auditory Verbal Learning Test.

Tubes containing samples are labeled with the participant’s code, trial ID, and date for accurate identification. From the collected blood samples, 4 mL is routed to the chemical pathology laboratory for blood biochemistry analysis. The remaining samples are stored appropriately on ice or in a 4 °C refrigerator until they undergo centrifugation, facilitating the isolation of plasma samples. These collected plasma samples are apportioned into 1-mL storage tubes and immediately stored in a –80 °C freezer. This storage method ensures that the samples are preserved for the analysis of oxidative stress markers (MDA, AGE, F2-IsoPs, and PC), inflammatory markers (TNF-α and IL-6), vitamin E, and appetite regulation markers (leptin and ghrelin), all to be conducted within 12 months of storage (Table 1).

**Table 1 table1:** Summary of tests performed at 0, 3, and 6 months.

Number and time points, category, and parameters			Sample		Methodology	
**(1) Screening**						
	**Blood biochemistry tests**					
		Liver function (ALT^a^, ALP^b^, albumin, protein, bilirubin)	Blood		Clinical chemistry analyzer	
		Lipid profile (TG^c^, HDL^d^, LDL^e^, cholesterol)	Blood		Clinical chemistry analyzer	
		Renal function (Na, K, Cl, urea, creatinine)	Blood		Clinical chemistry analyzer	
		Full blood count (WBC^f^, RBC^g^, hematocrit, MCV^h^, platelets)	Blood		Clinical chemistry analyzer	
		Fasting glucose	Blood		Clinical chemistry analyzer	
		C-reactive protein	Blood		Clinical chemistry analyzer	
	**Physical examination**					
		Blood pressure	—^i^		Blood pressure monitor	
		Heart rate	—			
		BMI	—		Body weight scale and stadiometer	
	**Past medical history**					
		Medications	—		Screening form	
		Supplements	—		Screening form	
		History of illness	—		Screening form	
	**Social history**					
		Smoking	—		Screening form	
		Alcoholic consumption	—		Screening form	
		Exercise	—		Screening form	
		Dietary patterns	—		Screening form	
**(2) 0, 3, and 6 months**						
	**Physical examination**					
		Blood pressure	—		Blood pressure monitor	
		Heart rate	—			
		BMI	—		Body weight scale and stadiometer	
	**Body composition measurements**					
		BMI	Whole body		Body composition analyzer	
		Segmental and visceral fat	Whole body		Body composition analyzer	
		Basal metabolic rate	Whole body		Body composition analyzer	
	Blood biochemistry tests			Blood		Clinical chemistry analyzer
	**Oxidative stress markers**					
		AGEs^j^	Blood		ELISA^k^ kit	
		PC^l^	Blood		ELISA kit	
		F2-IsoPs^m^	Blood		ELISA kit	
		MDA^n^	Blood		HPLC^o^	
	**Inflammation markers**					
		TNFα^p^	Blood		ELISA kit	
		IL-6^q^	Blood		ELISA kit	
	**Weight management**					
		Ghrelin	Blood		ELISA kit	
		Leptin	Blood		ELISA kit	
	Vitamin E level			Blood		HPLC
	**Skin assessment**					
		Elasticity	Face and arm		Cutometer	
		Hydration	Face and arm		Corneometer	
		Transepidermal water loss	Face and arm		Tewameter	
		Pigmentation	Face and arm		Mexameter	
		Sebum secretion	Face and arm		Sebumeter	
		Wrinkles and roughness	Face and arm		Visioscan	
**(3) 0 and 6 months**						
	Arterial stiffness assessment			Whole body		Arteriograph device /photoplethysmography
	Bone density assessment			Whole Body		Dual-energy x-ray absorptiometry
	**Cognitive function assessment**					
		MoCA^r^	—		Questionnaires	
		RAVLT^s^	—		Questionnaires	
		Digit span test	—		Questionnaires	

^a^ALT: alanine transaminase.

^b^ALP: alkaline phosphatase.

^c^TG: triglycerides.

^d^HDL: high-density lipoprotein.

^e^LDL: low-density lipoprotein.

^f^WBC: white blood cells.

^g^RBC: red blood cells.

^h^MCV: mean corpuscular volume.

^i^Not applicable.

^j^AGEs: advanced glycation end products.

^k^ELISA: enzyme-linked immunosorbent assay.

^l^PC: protein carbonyl.

^m^F2-IsoPs: F2-isoprostanes.

^n^MDA: malondialdehyde.

^o^HPLC: high-performance liquid chromatography.

^p^TNFα: tumor necrosis factor-α.

^q^IL-6: interleukin-6.

^r^MoCA: Montreal Cognitive Assessment.

^s^RAVLT: Rey Auditory Verbal Learning Test.

Furthermore, the assessment of arterial stiffness is conducted by skilled laboratory assistants using arteriography during the participants’ visits at both the 0- and 6-month time points. This assessment uses inflatable cuffs and is noninvasive. The arteriograph primarily measures pulse wave velocity, augmentation index, and central blood pressure, all of which reflect vascular health. Total body fat and lean mass measurements are accomplished using an InBody device during the participant visits at 0, 3, and 6 months.

In addition, skin health is analyzed using a Cutometer (Courage+Khazaka electronic GmbH) and Visioscan (Courage+Khazaka electronic GmbH) during participant visits at 0, 3, and 6 months. At 2 anatomical locations (volar side of the forearm and lateral periorbital region of the face), skin characteristics such as elasticity, hydration, transepidermal water loss, pigmentation, sebum secretion, wrinkles, and roughness will be studied. At both locations, 4 to 5 repeated measurements are made for each parameter, and the results are averaged. To ensure site uniformity and accommodate anatomical changes, slight positional deviations of a few centimeters are permitted. By measuring at the forearm and face, it is possible to conduct a thorough analysis of skin alterations in regions with low and high levels of sun exposure, respectively. This increases sensitivity to both the local and systemic effects of the intervention.

Subsequently, for secondary outcome measures, participants undergo cognitive function assessments, which include the MoCA, RAVLT, and digit span test. These assessments are performed with the assistance of a trained research assistant during the participants’ visits at 0 and 6 months. Finally, the measurement of bone mineral density is conducted using a dual-energy X-ray absorptiometry device at 0 and 6 months. Full body, lumbar spine, and hip scans are conducted. The lumbar spine and hip are essential locations for measuring bone density in older adults, which is crucial for comprehending how tocotrienol supplementation affects bone health. These regions are significant to the study since they represent general bone health.

To monitor changes in dietary habits, participants complete a food frequency questionnaire during their visits at 0, 3, and 6 months. The food intake checklist was developed to monitor changes in dietary habits throughout the study. Nutritionist Pro software is used to analyze the diet history data for each participant to quantify their nutrient intake values. Statistical analysis is then conducted to determine whether the nutrient value is significantly different from the blood biochemistry composition. Figure 1 presents a flowchart illustrating the study period and the tests conducted at each time point.

### Participant Timeline

Over the study period, 3 assessments are carried out at 0, 3, and 6 months across various domains of inquiry, encompassing oxidative stress, inflammation, skin conditions, arterial stiffness, cognitive function, appetite regulation, bone mineral density, and vitamin E levels. To ensure comprehensive oversight of the assessments, delegation of an authority log was established and formally endorsed by the respective investigators, each of whom possesses expertise in their specific area of assessment.

### Sample Size

Sample size estimation was based on a comparison of mean low-density lipoprotein levels, referencing a previous case-control study on biomarkers for premature coronary artery disease by Shukor et al [99]. The sample size was calculated using a power and sample size program. The effect size was calculated based on a mean value of 3.11 (SD 0.81) for group one and a mean value of 2.66 (SD 1.25) for group two.

The total number of required participants calculated per group of the experimental design was 93 when dichotomous outcomes were presumed with a Type I error probability, α of .05, and power of 0.8. To maintain the power, a 20% dropout rate was factored in. Consequently, 110 participants are required to be enrolled in each group (placebo and supplementation). Therefore, a total of 220 participants are required to perform this clinical study.

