On average, the screening process typically lasts around 2 hours. According to the latest data, approximately 60% of the volunteers successfully met the inclusion criteria and became eligible for recruitment into the study. The primary reasons for volunteer exclusions were elevated levels of total cholesterol, low-density lipoprotein cholesterol, fasting blood glucose, and blood pressure. On average, each participant requires approximately 3 hours to complete all assessments, excluding blood tests. To accommodate the fasting requirement for blood withdrawal and arterial stiffness assessment, these tests are conducted first. Subsequently, the remaining assessments are performed simultaneously at different stations, allowing participants to visit any available station. To minimize the waiting time, a maximum of 5 participants are scheduled per sampling day. This ensures that participants do not experience prolonged waiting periods.

Throughout the treatment period, the research assistants monitor the compliance of the participants through regular phone calls and short messages. However, the effectiveness of this monitoring method relies on the participants’ availability to respond to or read the messages. Noncompliant cases were primarily attributed to participants’ difficulty with remembering to take the supplement, which is evident when they return the bottles with a higher number of remaining softgels than expected during the 3- and 6-month visits. The data from noncompliant participants are still analyzed. However, it is specifically noted in the CRF so that any potential outliers in data analysis can be identified later.

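### The sample-size paragraph contradicts itself: it sizes LDL means but calls the outcome dichotomous, and 93 per group with 20% dropout does not give 110

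*Protocol article*

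**What the plan says.** All the figures stand in the Sample Size section of the protocol article.

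- Basis: "Sample size estimation was based on a comparison of mean low-density lipoprotein levels", taken from an earlier case-control study of biomarkers for premature coronary artery disease.
- Inputs: "a mean value of 3.11 (SD 0.81) for group one and a mean value of 2.66 (SD 1.25) for group two".
- Error rates: "with a Type I error probability, α of .05, and power of 0.8". Sidedness is not given.
- Result: "The total number of required participants calculated per group of the experimental design was 93 when dichotomous outcomes were presumed". No proportions are given.
- Dropout: "To maintain the power, a 20% dropout rate was factored in. Consequently, 110 participants are required to be enrolled in each group", for a total of 220.

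The Analyses section repeats 220. It adds that anyone who withdraws or is removed is replaced so that the total stays there, with 110 on each product. The planned analysis is a mixed-design ANOVA on means, by intention to treat.

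**The concern.** Three steps of the derivation look wrong.

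1. A comparison of two means with SDs is not a calculation for a dichotomous outcome, and without proportions no binary calculation can be attempted.
2. The figure of 93 is not what the usual two-sample formula returns from the printed means and SDs.
3. The step from 93 to 110 does not match the stated 20% allowance, although the text says that the allowance keeps the power.

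This is the only justification the article gives for 220 participants. As it stands, a reader cannot tell which evaluable number the design aims for, or what LDL difference it can detect with 80% power. The difference used is also a contrast between study groups in a case-control study, so it should not be read as the effect expected of the supplement.

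**Working it through.** **Inputs** (Sample Size section): means 3.11 and 2.66; SDs 0.81 and 1.25; alpha .05; power 0.80; 20% dropout; equal groups. Two-sided testing is my assumption, and the one-sided results are shown as well.

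**Step 1. Attempt to reproduce 93.**

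- Difference = 3.11 − 2.66 = 0.45.
- Equal-weight pooled SD = √[(0.81² + 1.25²)/2] = √[(0.6561 + 1.5625)/2] = 1.053.
- Standardised difference = 0.45/1.053 = 0.427.
- Normal approximation: n per group = 2 × [(1.960 + 0.842)/0.427]² ≈ 86.
- The noncentral t calculation gives **87**.

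Other SD choices, by the t test at 80% power:

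| SD used | two-sided | one-sided |
|---|---|---|
| 1.053 (equal-weight pooled) | 87 | 69 |
| 1.03 (simple average) | 84 | 66 |
| 0.81 (group one only) | 52 | 41 |
| 1.25 (group two only) | 123 | 97 |

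None of these is 93.

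**Step 2. What would give 93?** A two-sided t test needs 93 per group when the SD is about 1.09. A pooled SD weighted by group size can reach that. With a share w of the weight on the SD 1.25 group, SD = √[(1 − w) × 0.6561 + w × 1.5625]. At w = 0.58 this is √(0.2756 + 0.9063) = 1.087, and the required n is 93. At w = 0.50 it is 87, and at w = 0.60 it is 94. The source study's group sizes are not printed, so w is unknown.

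**Step 3. The dropout allowance.** This step does not depend on how 93 arose.

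- Needed to keep 93 after 20% loss: 93/(1 − 0.20) = 116.25, so 117 per group (234 in total).
- Simple multiplication, the common shortcut: 93 × 1.2 = 111.6, so 112.
- Left from 110 after 20% loss: 110 × 0.80 = 88.
- Loss that 110 can bear while keeping 93: 1 − 93/110 = 15.5%.
- Starting from 87 instead: 87/0.80 = 108.75, so 109, close to the stated 110.

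**Step 4. Power for a difference of 0.45** (two-sided t test).

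| Evaluable per group | SD 1.053 | SD at which 93 gives 80% |
|---|---|---|
| 88 | 80.5% | 77.8% |
| 93 | 82.6% | 80.0% |
| 110 | 88.4% | 86.2% |

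**The case against.** **The figure of 93 may be right.** The inputs come from a case-control study, where unequal groups are common, and the usual pooled SD weights by group size. With about 58% of the weight on the group with SD 1.25, the program would return 93. This stands. A reader might infer from Step 1 that 93 is an error for 87, but the article does not support that. It shows only that 93 cannot be checked from what is printed. Replacing 93 with 87 unseen could swap a correct program output for an assumption.

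**Withdrawals are replaced.** The Analyses section does not simply let 110 shrink to 88, and the intention-to-treat analysis with mixed models uses incomplete participants too, so 88 is a pessimistic basis for power. This softens the shortfall. It does not repair the paragraph, which derives 110 from a dropout allowance and not from replacement. If replacement really kept 110 completers per group, the allowance would serve no purpose.

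**Power is about 80% anyway.** On equal-weight pooling, yes. A reader might infer from the mismatch that the trial is underpowered for LDL. The figures do not show that: the worse of the two coherent readings gives 77.8%. A lower figure of about 66% at 88 per group needs SD 1.25 in both groups, which contradicts the stated 0.81.

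**The source of the effect is disclosed.** It is, and choosing it is a design judgement. The Discussion reports that "The primary reasons for volunteer exclusions were elevated levels of total cholesterol, low-density lipoprotein cholesterol, fasting blood glucose, and blood pressure", so enrolment is selective on the sizing variable. No LDL distribution is given, however, so the effect of this on the SD cannot be quantified. What remains is a matter of labelling.

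**Conclusion.** The concern holds as an error in stated figures. The dichotomous label contradicts the comparison of means beside it. The numbers 93, 20% and 110 cannot all be right: 110 is 7 per group short of 117, or the allowance is 15.5% and not 20%. Neither conclusion depends on an assumption about the SD or sidedness.

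That 93 is not reproducible holds for every SD choice in the table, one- or two-sided. That 93 is wrong is not established, because it depends on source group sizes that are not given.

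The practical size is small. For a difference of 0.45 at two-sided 5%, 88 evaluable per group gives between 77.8% (if 93 is the true requirement) and 80.5% (if the SDs were pooled with equal weight). This is a correction of the published justification, and no evidence of a material lack of power for LDL.

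**What to change.** Correct the Sample Size paragraph and keep the total at 220.

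1. Delete the word dichotomous.
2. From the saved program output, state the test, the sidedness, the SD used and how it was pooled, including the source group sizes if they were used as weights.
3. Make the chain agree with that output:
   - If 93 is confirmed, either restate the dropout allowance as about 15%, or keep 20% and state about 78% power at 88 per group.
   - If equal-weight pooling was used, replace 93 with 87. Then 87/0.80 = 109, rounded to 110, with about 80% power at 88 per group.
4. Describe 0.45 as the difference the trial can detect, since it is a case-control contrast and not an observed effect of the supplement.
5. State how the replacement of withdrawals in the Analyses section relates to the dropout allowance.

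The cost is one paragraph and a look at the program output. Enrolment and analysis do not change.

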### Recruitment

The selection of potential trial participants is conducted by the PI based on the inclusion and exclusion criteria. Participants who fail to meet the inclusion and exclusion criteria are defined as screening failures. The PI maintains a Screening Log, which includes screen failures to ensure a systematic selection of participants. Informed consent is obtained from each participant by the contract research assistants. During enrollment, general information (name, gender, age, address, and contact information) is obtained. To ensure security and confidentiality, each participant is assigned a participant-specific code. The code is used to label the participant’s laboratory results. Each participant is reimbursed for standard transportation fees.

Participants are free to withdraw from the study at any time for any reason. Participants may also be withdrawn at any time at the discretion of the PI. Possible reasons for withdrawal include abnormal laboratory values, protocol violation, the participant requiring the use of an unacceptable concomitant medication, participant not complying with protocol procedures, participant developing a condition during the study that violates the inclusion or exclusion criteria, loss to follow-up, death, or any other reason in the PI’s opinion that would impede participation in the study.

### Assignment of Interventions

Tocotrienols and placebo supplements are prepared and labelled with the IP number by the sponsor. Assignment of supplements to participants is by chance through the drawing of lots by contract research assistants. The treatment is double-blinded throughout the study period until all data have been collected and analyzed, after which the supplementation IP numbers are revealed to the PI by the sponsor. However, in case of any serious adverse event reported during the study period, the unmasking of the code is immediate.

A set of numbers, from 1 to 60, is randomized using the randomization application for every block of 60 participants. The participants are assigned a randomized number according to the numerical sequence 1 to 60 in the list of randomized numbers. All even numbers are treated with the same IP, while odd numbers are treated with another IP. Thus, every block randomization has an equal number of participants for each IP. The randomization will be repeated until 220 participants are recruited.

The unblinding in emergency situations is only permitted in case of a suspected, unexpected serious adverse reaction or other important adverse event, when knowledge of the supplemented product in question is required for therapeutic decisions in the medical management of the participant.

In the event of an emergency, an emergency decoding option is accessible to both the PI and designated personnel at the sponsor. The responsibility for breaking the blind for individual participants in emergency situations lies with the PI. If the need to break the blind arises, the PI will communicate this to the sponsor. Before the treatment code is broken, the PI responsible for unblinding must document the reason and date for unblinding in the case report form (CRF) to ensure proper documentation of the unblinding event, including a clear explanation of the reason for unblinding.

In the event that the sponsor requires unblinding of the treatment, the reason and date of unblinding are recorded in the CRF. In situations where it is necessary to unblind an individual participant’s treatment for the purpose of expedited reporting to the authorities, only designated individuals at the sponsor who are responsible for reporting this information will have access to the identity of the product. Every effort is made to ensure that all other members of the clinical trial remain blinded throughout the entire duration of the trial.

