### Analyses

Statistical analysis is conducted using SPSS (IBM Corp). The Kolmogorov-Smirnov test will be performed to assess the normality of the data distribution. Type III sum of squares is set to evaluate the hypotheses.

A mixed-design ANOVA will be used to determine whether supplementation affects the blood biochemistry parameters (inflammation and oxidative stress) and physical health (body composition, skin, cognitive function, and vascular health) at baseline, 3 months, and 6 months among the groups. The Mauchly test of sphericity will be conducted to assess homogeneity of variance and compare the means of the supplemented group with those of the placebo group. To account for the risk of a Type I error as a result of many primary and secondary outcomes, multiplicity correction procedures will be used. In particular, the Benjamini-Hochberg approach for false discovery rate control will be used in each outcome domain (eg, oxidative stress markers, inflammatory markers, cognitive tests). Statistical power and Type I error control are balanced for exploratory research in this method with connected variables. The Tukey post hoc test will be used for comparisons between groups, while the Dunnett test will be used for comparisons within groups over time. In terms of missing data, linear mixed-effects models with the missing at random assumption will be used, which is acceptable given the repeated-measures design and inclusion of observed predictors. Nevertheless, dropout rates in older adult groups might differ from missing at random (for example, because of undetected health decline). To evaluate the possible impact of data missing not at random, sensitivity analyses will be conducted using pattern-mixture models and multiple imputation with delta-adjustment scenarios. These methods aid with determining the robustness of the findings under alternate missingness assumptions. All data will be presented as mean (SD), with statistical significance defined as *P*<.05.

This study requires a total of 220 volunteers as calculated using the power and sample size program. In the case where any participant withdraws or is eliminated during the course of the project, their ID number is not reused. Instead, new volunteers are recruited to maintain the total sample size at 220. The distribution of the IP numbers is rerandomized and adjusted as needed to ensure that both groups remain equally balanced, with 110 participants receiving each IP.

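### Assignment is described in two unreconciled ways, and 110 per product is secured by adjusting the allocation, since blocks of 60 do not guarantee it at 220

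*Protocol article*

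**What the plan says.** All references are to the protocol article.

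- **Assignment of Interventions, first paragraph:** "Assignment of supplements to participants is by chance through the drawing of lots by contract research assistants".
- **Assignment of Interventions, second paragraph:** "A set of numbers, from 1 to 60, is randomized using the randomization application for every block of 60 participants". Participants take these numbers in list order. "All even numbers are treated with the same IP, while odd numbers are treated with another IP".
- **Same paragraph, on balance and stopping:** "Thus, every block randomization has an equal number of participants for each IP. The randomization will be repeated until 220 participants are recruited".
- **Sample Size:** 110 participants are to be enrolled per group, 220 in all.
- **Analyses:** withdrawn participants' IDs are not reused, new volunteers are recruited to hold the total at 220, and the IP numbers may be randomized afresh and adjusted so that the groups stay equal, "with 110 participants receiving each IP".
- **Interventions:** the contract research assistants generated the sequence, and they also enroll participants and assign them.

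**The concern.** Under a pre-generated list the next assignment is settled before the participant arrives, and any departure from it can be found afterwards. Under a draw of lots by staff, an act at the time of assignment decides. Either can be random, but they are different procedures with different safeguards, and the text gives both as the way a participant receives a product.

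The second issue is the equal split. The text presents equality as a property of the blocks, but enrollment stops inside a block. What delivers 110 per IP is the adjustment rule in Analyses. A rule that lets the allocation be altered to reach a target count gives discretion over individual assignments. Here that discretion would lie with the people who hold the sequence and decide whom to enroll. What is at stake is the claim, made in the Discussion, that randomization gave an unbiased allocation.

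**Working it through.** **1. The two mechanisms side by side.** The list fixes the order by application, in blocks of 60, with odd or even deciding the IP. The lots sentence says staff draw lots to assign supplements to participants. No sentence says that lots were used for one step only (for example, which IP is even) or that the lots are the list under another name. The Results section reports that the first 120 participants were evenly divided. That fits two full blocks (120 = 2 × 60) but does not settle the question.

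**2. The stated balance in full blocks.** The numbers 1 to 60 contain 30 even and 30 odd, so a full block gives 30:30. The statement "Thus, every block randomization has an equal number of participants for each IP" is correct for full blocks.

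**3. Stopping at 220.** 220 = 3 × 60 + 40. The three full blocks give 90:90. The fourth stops after 40 of its 60 places.

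**4. The split in the incomplete block.** Inputs: N = 60 numbers, K = 30 even, n = 40 used. The count X of even numbers is hypergeometric.

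- Mean = 40 × 30/60 = 20.
- Variance = 40 × 0.5 × 0.5 × (60 − 40)/(60 − 1) = 10 × 20/59 = 3.39, so SD = 1.84.
- P(X = 20) = C(30,20) × C(30,20) / C(60,40) = 0.215. This is the chance of exactly 110:110.
- P(112:108 or worse) = 0.412; P(113:107 or worse) = 0.170; P(114:106 or worse) = 0.054; P(115:105 or worse) = 0.013.
- The 2.5th and 97.5th percentiles of X are 16 and 24, so arm totals run from 90 + 16 = 106 to 90 + 24 = 114. The extremes of X are 10 and 30, giving 100:120 or 120:100.

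**5. If lots meant independent draws.** For 220 independent even-chance draws, SD = √(220 × 0.25) = 7.42, and P(110:110) = 0.054. The two descriptions can therefore imply quite different degrees of balance.

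**6. What imbalance costs.** Efficiency relative to 1:1 is 4·n₁·n₂/N².

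- 114:106 gives 4 × 114 × 106 / 220² = 48,336/48,400 = 0.999.
- 120:100 gives 48,000/48,400 = 0.992.

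**7. Limits of step 4.** It assumes exactly 220 are randomized. Because withdrawals are replaced, the number randomized can exceed 220, and the last block then stops elsewhere or completes (240 would give 120:120). With m places used in the last block, variance = (m/4) × (60 − m)/59. This is largest at m = 30, where it is 7.5 × 30/59 = 3.81 (SD 1.95). The imbalance stays of the same small order wherever enrollment stops, but a fixed range of 106 to 114 would not be right.

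**8. Timing.** The Results section gives 211 recruited by April 2025 (the Abstract gives 209). 211 = 3 × 60 + 31 and 209 = 3 × 60 + 29. If numbers were used in order, the fourth block was open on either count, and its last assignments were still to come.

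**The case against.** The strongest defence has four parts.

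- **The lots sentence may be loose wording.** It could be a lay summary of random assignment, or describe a single step, in a condensed article. Drawing 60 numbered lots without replacement would give 30:30, and a draw can be recorded. This stands against any claim that the two accounts are proven incompatible, or that lots would be biased or impossible to audit. It does not remove the need to reconcile them, because the sentence says that lots assign supplements to participants.
- **Equal arms are not impossible.** A reader might infer that blocks of 60 cannot give 110 per IP. That is too strong: full blocks are equal as stated, and 110:110 arises by chance about one time in five. The supportable statement is that the scheme does not guarantee it.
- **The article says how 110 is reached.** The Analyses section does state an adjustment rule, in the context of replacing withdrawals. This is true, but the rule is the weaker part of the design: it departs from the list to correct an imbalance that costs almost no power.
- **Product content is masked.** Softgels look alike and carry only an IP number, which limits how purposefully anyone could steer. This reduces the risk without removing it, since those assigning still work with two distinguishable IP numbers.

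The block arithmetic alone is a minor matter, and few assignments may remain.

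**Conclusion.** The point holds in a limited form. The article gives two unlinked assignment mechanisms. Its block scheme does not guarantee equal numbers in the last block or 110 per IP: the chance of exactly 110:110 is about 21.5%, with a 95% range of 106 to 114 per arm, assuming the list is followed and exactly 220 are randomized. The figure of 110 is secured only by a rule permitting adjustment of the allocation, operated in a setting where the same staff generate the sequence, enroll and assign.

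A reader might go further and infer that assignments were in fact steered, or that lots compromised the randomization. The document shows neither. It shows an unclear mechanism and a rule that leaves room for steering without any statistical gain. The loss of power from leaving the arms unequal is negligible. The weight of the finding lies in how trustworthy the allocation is, and the correction is worth making while the last assignments may still be open.

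**What to change.** 1. In Assignment of Interventions, state which mechanism assigned participants and reconcile the two sentences. If any participants were assigned by another method, disclose how many and when.
2. State that every participant, including each replacement, receives the next entry on the pre-generated list.
3. In Analyses, delete the provision for randomizing IP numbers again and adjusting them to equalize the groups.
4. Replace the statements that every block is equal and that 110 receive each IP with wording that the groups are approximately equal because the last block may be incomplete. Give no fixed range, since replacements can take the number randomized above 220.

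The cost is wording and a short disclosure. The arms may finish a few participants apart, which by the calculation above loses under 1% of efficiency even at 120:100.
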